## Overall sample size

Currently, the percentage of pregnant patients who are being diagnosed with COVID-19 is unknown, this being one of the objectives of the study. The registry includes 100 sites that in 2019 cared for a total of 172,000 deliveries (Appendix 1 and 3).

## Data sources and work plan

### Patient referral sources

If the doctor in charge considers it appropriate to inform the patient about the existence and purpose of this registry, he/she may do so. At this time, consent will be requested so that the information derived from the regular monitoring of these patients is incorporated into the data registry, and that said information can be analysed and disclosed for scientific purposes in accord with the confidentiality provisions of the current legislation.

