## Abstract

**Rationale:** Knowledge about the impact of the SARS-CoV-2 virus on pregnancy is still scarce and all current recommendations are based on less than 100 cases published in the literature. To identify moderate effects (such as vertical transmission, obstetric morbidity, foetal death, maternal or neonatal death) and to allow accurate risk estimates, larger sample sizes than those currently available are required.

**Methods:** Prospective observational study of pregnant women in whom SARS-CoV-2 infection is suspected at any time during pregnancy with positive test results for SARS-CoV-2, in order to create a registry of baseline characteristics of the pregnant woman, aspects related to the course of pregnancy and delivery, and related to the new-born, with an observation period of up to 14 days after delivery. Subsequently, several phased studies will be conducted to help establish and monitor the set of measures to improve the care of pregnant women.

**Discussion:** The national registry for COVID-19 in pregnancy described here is a tool for sharing and centralizing data related to exposures to SARS-CoV-2 during pregnancy in a structured way. It should speed up the process of prospectively obtaining a large unbiased data set and will collect information at national level.

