## Rationale

To date, few studies have described the impact of the SARS-CoV-2 virus on pregnancy, particularly infection occurring during the third trimester of pregnancy. The impact of the virus during the first and second trimesters of pregnancy remains unknown and must be urgently determined. All current recommendations are based on less than 50 cases published in the literature, with speculations on different aspects of management. To identify moderate effects (such as vertical transmission, foetal death, maternal or neonatal death), larger sample sizes than those currently available are required to allow accurate risk estimates. The national registry for COVID-19 in pregnancy described here is a tool for sharing and centralizing data related to exposures to SARS-CoV-2 during pregnancy in a structured way. It should speed up the process of prospectively obtaining a large unbiased data set and will collect information at national level.

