## Study population and selection criteria

For the characterization of the clinical course of SARS-CoV-2 infection during pregnancy, the pre-study sample size calculation has not been carried out, as registry-based studies generally tend to be comprehensive without involving hypotheses.

Patients eligible for follow-up of target population will be any pregnant woman who is suspected or needs to be ruled out as having a SARS-CoV-2 infection at any time during pregnancy with positive test results for SARS-CoV-2 by PCR.

Information regarding each pregnant woman's demographic characteristics, comorbidities and current obstetric history was extracted from the medical history and the patient interview; subsequently, age and race were categorized according to the classification used by the Center for Disease Control and Prevention (CDC) (17).

For the selection of the control group to be collected in the same database, patients with a negative COVID-19 delivery diagnosed by PCR screening at delivery, or less than 3 days before, were considered.

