### Data collection

Encrypted health-related personal data is collected prospectively using the **OBS Covid Spain** database of the company ReserArch.

The collection of data on each pregnant woman is planned from the diagnosis of a case in a pregnancy up to 6 weeks after delivery and up to 14 days postpartum in the case of the new-born, based on a manual prepared for the collection of data and for the investigator.

Hospitals enrol their pregnant patients on an ongoing basis, and the information is collected and stored anonymously in two separate phases: the first phase, during the inclusion period that occurs at the time of the SARS-CoV-2 test in the pregnant woman; the second phase, throughout the 2 weeks after birth.

For sites with existing cohorts using methods that comply with registry data collection methods (i.e., systematic inclusion of women screened for SARS-CoV-2 regardless of test results, prospective follow-up, and information

requested as shown in the variables table of appendix 5), the data collected will be entered at the time they join the registry.

Delivery monitoring: the *outcomes* include perinatal and neonatal events, which were collected at the time of delivery and the days immediately afterward. These perinatal events included gestational age, type of delivery, presence of prepartum or premature rupture of membranes before delivery, as well as any medical complications (thromboembolic events, admission to ICU, maternal death) and obstetric complications (hemorrhagic events and hypertensive disorders), while neonatal events included the 5-minute Apgar score, the pH of the umbilical artery and possible complications such as admission to the NICU and neonatal death in the follow-up period or intrauterine foetal death. The definitions of obstetric pathology follow the international criteria of the ACOG and RCOG (18-21).

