## Informed consent

In accordance with the criteria of good clinical practice, the subjects will be duly informed of all those details concerning their participation in the study and will freely give their consent in writing or orally, recording this fact in their medical records.

Preferably written or oral consent will be sought for cases and controls chosen at random from among pregnant women who have given birth in each centre and who have COVID-19. The patient may sign the consent electronically (See appendix 7).

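### The offer of the registry is left to the treating doctor and the consent section adds an incompatible rule, so the protocol permits outcome-related selection of cases into data it calls unbiased

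*Protocol*

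**What the plan says.** **How a woman is approached.** In the Protocol, the section Patient referral sources opens with this rule: "If the doctor in charge considers it appropriate to inform the patient about the existence and purpose of this registry, he/she may do so". The next sentence ties consent to that moment: "At this time, consent will be requested so that the information derived from the regular monitoring of these patients is incorporated into the data registry". A woman who is not told is not asked.

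**When she enters.** Protocol, Data collection, describes two phases of collection: "the first phase, during the inclusion period that occurs at the time of the SARS-CoV-2 test in the pregnant woman", and a second phase in the two weeks after birth. For sites that bring an existing cohort, the same section names as compliant with registry methods "systematic inclusion of women screened for SARS-CoV-2 regardless of test results, prospective follow-up".

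**Who is asked for consent.** Protocol, Informed consent, seeks it from "cases and controls chosen at random from among pregnant women who have given birth in each centre and who have COVID-19".

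**Who the controls are.** Study population and selection criteria, and Substudy 3 (Patients), take controls from women who are PCR-negative at delivery or less than 3 days before. Substudy 3 selects them as deliveries adjacent to the case, at most 3 per case.

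**What is claimed.** The Abstract says of the registry: "It should speed up the process of prospectively obtaining a large unbiased data set". The Rationale repeats the sentence. Secondary objectives include the incidence of diagnosed infection in pregnant women in Spain and the risks of ICU admission, death, miscarriage and stillbirth.

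**The concern.** Incidence and risk estimates from a registry depend on who gets in. If the offer rests on individual judgement, a doctor who already knows how ill the woman is, or how the pregnancy ended, can let that knowledge affect whether she is asked. One site may enrol its memorable severe cases, another the mild ones who are easy to approach. Neither would be departing from the text.

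The sentence under Informed consent makes this worse, because a site cannot follow it together with Data collection. With 100 sites, different readings would produce differently composed case groups. At stake are the registry's risk proportions and the case side of the comparison in Substudy 3, where controls are found by reference to each case. A larger registry narrows the confidence intervals but leaves such a bias in place.

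**Working it through.** The protocol gives no figure on this point, so there is nothing to reproduce. The check compares the sections and then works a hypothetical.

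**1. Is there a rule that every eligible woman be approached?**
- Study population and selection criteria defines who is eligible, not who is offered entry.
- Data collection says hospitals enrol on an ongoing basis, which does not mean all women or consecutive women. Its standard of systematic inclusion is stated only for sites joining with existing cohorts.
- Substudies 1 and 2 (Patients) restate eligibility and give no sampling rule.
- Substudy 3 (Design) refers to universal, consecutive PCR screening. That describes hospital testing, not enrolment.
- Substudy 4 (Design) draws from its own random list, so it has a rule.

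For newly enrolled women in the registry and for the cases of Substudies 1 to 3, no such rule is found.

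**2. Does the consent sentence fit the other sections?**

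| Feature | Informed consent | Elsewhere in the Protocol |
|---|---|---|
| Time of entry | After birth | At the test (Data collection) |
| Choice of controls | Random | Adjacent deliveries, at most 3 per case (Substudy 3, Patients) |
| Status of controls | Read literally, with COVID-19 | PCR-negative (Study population; Substudy 3) |
| Pregnancies without a birth | Outside the pool | Miscarriage and maternal death are outcomes (Secondary objectives 5 and 6) |

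It conflicts on every row. A random draw does not itself bias. The difficulty lies in the pool it draws from and in the clash with the other rules.

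**3. How much could selection matter? (hypothetical)**

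Let p be the true risk among PCR-positive women. Let r be the chance of being offered entry for women with the outcome, divided by that for women without it. If acceptance is equal in the two groups,

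observed risk = p·r / (p·r + 1 − p).

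Both p and r are assumptions; the document gives neither. With p = 3%:
- r = 2: 0.06 / (0.06 + 0.97) = 5.8%. Per 100 women, all 3 with the outcome and half of the other 97 are offered entry: 3/51.5.
- r = 0.5: 0.015 / (0.015 + 0.97) = 1.5%. Per 100 women: 1.5/98.5.

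Over r = 0.5 to 2, the observed risk runs from 1.0% to 3.9% when p = 2%, from 2.6% to 9.5% when p = 5%, and from 5.3% to 18.2% when p = 10%. A milder r of 0.8 to 1.25 at p = 5% gives 4.0% to 6.2%. With r = 1 there is no bias in the risk.

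For a crude odds ratio in Substudy 3, if controls enter independently of outcome, the odds of the outcome among cases are multiplied by r, and so is the odds ratio.

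**The case against.** **Discretion biases a risk only if it is related to outcome, and at the test the outcome is usually still ahead.** The first half is correct, which is why the hypothetical gives no bias at r = 1. The second half holds for women tested early in pregnancy. It is weaker for women tested because they are already ill or screened at delivery, when severity or outcome may be known at the test or soon after. Nor does the text tie the doctor's decision to the time of the test.

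**The consent sentence is garbled and is not the selection rule.** It is poorly worded, and the random choice may be meant for controls only. It is therefore weak evidence that sites actually enrol only after birth. It remains an instruction on whom to ask for consent, and it has to be reconciled with the other sections.

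**A manual may fill the gap.** Data collection mentions one that is not shown. It might require consecutive approach, but that would contradict the permissive sentence in the Protocol.

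**Heterogeneity between sites will be examined.** Heterogeneity tests can show that sites differ. They cannot recover women who were never offered entry.

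**Consent is voluntary.** That limits who accepts. It does not require the doctor to choose who is asked.

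A reader might infer that the doctor's discretion is the only way into the data, that the registry is demonstrably a selected sample, or that every proportion is biased. The document does not support these readings. Existing cohorts may enter with systematic inclusion, Substudy 4 has its own random list, and permission to select is not proof of selection. Nor does the remark that "registry-based studies generally tend to be comprehensive without involving hypotheses" describe this data set. It is a general reason for having no sample size calculation. The direct claim is that of unbiased data.

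**Conclusion.** The point holds as a fault in the enrolment rules. The offer of the registry is discretionary, nothing requires that newly enrolled eligible women be approached consecutively, and the consent sentence contradicts the stated time of entry and the definition of controls. This does not support a promise of unbiased data. It leaves the case group of the registry and of Substudies 1 to 3 open to outcome-related selection. Substudy 4's sampling is outside this conclusion.

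The direction and size of any bias cannot be derived from the document. The figures of 5.8% and 1.5% against a true 3% rest on an assumed risk and an assumed twofold difference. They show that such a difference would roughly double or halve a risk estimate. The gap between the two figures compares opposite extremes and should not be read as the expected error.

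**What to change.** 1. **Patient referral sources.** Replace the discretionary sentence with one rule: every pregnant woman with a positive PCR at the site is offered the registry consecutively, at the test result where possible, regardless of severity or outcome. Recruitment began on 1 March 2020 and this version cites a source accessed on 3 August 2020, so the rule cannot be applied backwards to women already entered. Flag those entered retrospectively so that they can be examined separately.
2. **Informed consent.** Correct the sentence so that consent is sought from all cases and from the PCR-negative controls identified by the adjacent-delivery rule of Substudy 3.
3. **Counts per site.** Have each site report the numbers of PCR-positive, approached, enrolled and excluded women. Give the exclusions by reason, including those under Exclusion criteria: inability to consent without a legal representative, the researcher's opinion, and loss of follow-up before 6 weeks postpartum. These exclusions limit capture even under a consecutive-offer rule.
4. **Claims.** Either show near-complete capture from these counts, or drop the description of the data as unbiased from the Abstract and Rationale and qualify the incidence and risk claims.

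The cost is protocol wording and one set of counts at each of the 100 sites, from laboratory or delivery lists. That is some work for the sites, but no extra tests. Oral and electronic consent are already allowed, which limits the burden of asking every woman.

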### Data collection

Encrypted health-related personal data is collected prospectively using the **OBS Covid Spain** database of the company ReserArch.

The collection of data on each pregnant woman is planned from the diagnosis of a case in a pregnancy up to 6 weeks after delivery and up to 14 days postpartum in the case of the new-born, based on a manual prepared for the collection of data and for the investigator.

Hospitals enrol their pregnant patients on an ongoing basis, and the information is collected and stored anonymously in two separate phases: the first phase, during the inclusion period that occurs at the time of the SARS-CoV-2 test in the pregnant woman; the second phase, throughout the 2 weeks after birth.

For sites with existing cohorts using methods that comply with registry data collection methods (i.e., systematic inclusion of women screened for SARS-CoV-2 regardless of test results, prospective follow-up, and information

requested as shown in the variables table of appendix 5), the data collected will be entered at the time they join the registry.

Delivery monitoring: the *outcomes* include perinatal and neonatal events, which were collected at the time of delivery and the days immediately afterward. These perinatal events included gestational age, type of delivery, presence of prepartum or premature rupture of membranes before delivery, as well as any medical complications (thromboembolic events, admission to ICU, maternal death) and obstetric complications (hemorrhagic events and hypertensive disorders), while neonatal events included the 5-minute Apgar score, the pH of the umbilical artery and possible complications such as admission to the NICU and neonatal death in the follow-up period or intrauterine foetal death. The definitions of obstetric pathology follow the international criteria of the ACOG and RCOG (18-21).

Follow-up after delivery: Patient follow-up is carried out by the local investigator over the phone and the medical history is consulted from the time the patient is discharged up to 6 weeks later in order to detect late postpartum complications related to COVID 19. In the case of the new-born, the follow-up is 14 days by the investigating neonatology department by telephone and consultation of the patient's medical history to detect symptoms of COVID 19 symptoms. Complications recorded in the mother during this period (mastitis, endometritis, pulmonary embolism) as well as neonatal death or readmission of the new-born due to COVID 19 were considered outcomes of interest and analysed together with those previously described.

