## Study design

Prospective observational registry study of pregnant women with suspected SARS-CoV-2 infection at any time during pregnancy with positive test results for SARS-CoV-2.

A specific database will be developed, which will include the baseline characteristics of the pregnant women, aspects related to the course of pregnancy and childbirth, and the new-born. Vertical transmission will be analysed only by means of a nasopharyngeal swab from the new-born before contact with the mother. This registry sets an observation deadline of up to 14 days after birth for the new-born and 6 weeks postpartum for the mother. The registry will be hosted on a secure https server, this server will be physically located at **OBS Covid Spain** of the company ReserArch which has a contract with the Puerta de Hierro-Majadahonda University Hospital Research Foundation.

Recruitment period will be between 1st March 2020 and 1st March 2021.

After that, different sub-analyses will be carried out with the data extracted in the registry and the secondary objectives will be addressed.

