#### Evaluation 14 days after delivery, N

|                                                   |                                 |
|---------------------------------------------------|---------------------------------|
|                                                   |                                 |
| Symptomatology, n (%)                      | Showing COVID-19 symptoms       |
|                                                   | Asymptomatic                    |
| COVID-19 symptoms                          |                                 |
| Mild symptoms (Symptoms reported at birth) | Cough                           |
|                                                   | Fever                           |
|                                                   | Dyspnoea                        |
|                                                   | New olfactory or taste disorder |
|                                                   | Fatigue/malaise                 |
|                                                   | Altered consciousness           |
|                                                   | Headache                        |
|                                                   | Nausea/vomiting                 |
|                                                   | Diarrhoea                       |
| Mild-moderate pneumonia                    |                                 |
| Severe pneumonia                           |                                 |
| Septic shock/maternal mortality            |                                 |

The rest of the variables are defined in appendix 5

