### Patients

Case eligibility criteria included individuals with laboratory confirmation of COVID-19 infection, irrespective of clinical signs and symptoms or the result of another serological test. Positive RNA PCR test from maternal nasopharyngeal swabs.

The selection of the control group will be collected in the same database, considering patients with negative COVID-19 delivery diagnosed by PCR screening at the time of delivery or less than 3 days before.

The delivery or deliveries that were treated in this site and that occurred within the same day, before and after the case (maximum 3 per case), are included in the control group. If the case were the last delivery of the day, the first ones of the following day could be recruited. If the case were the first of that day, the last one of the previous day could be recruited.

The data collected will be entered at the time they join the registry.

Delivery monitoring: the *outcomes* include perinatal and neonatal events, which were collected at the time of delivery and the days immediately afterward. These perinatal events included gestational age, type of delivery, presence of prepartum or premature rupture of membranes before delivery, as well as any medical complications (thromboembolic events, admission to ICU, maternal death) and obstetric complications (hemorrhagic events and hypertensive disorders), while neonatal events included the 5-minute Apgar score, the pH of the umbilical artery and possible complications such as admission to the NICU and neonatal death in the follow-up period or intrauterine foetal death. The definitions of obstetric pathology follow the international criteria of the ACOG and RCOG (18-21).

Follow-up after delivery: Patient follow-up is carried out by the local investigator over the phone and the medical history is consulted from the time the patient is discharged up to 6 weeks later in order to detect late postpartum complications related to COVID 19. In the case of the new-born, the follow-up is 14 days by the investigating neonatology department by telephone and consultation of the patient's medical history to detect symptoms of COVID 19 symptoms. Complications recorded in the mother during this period (mastitis, endometritis, pulmonary embolism) as well as neonatal death or readmission of the new-born due to COVID were considered *outcomes* of interest and analysed together with those described above.

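### The end of maternal outcome observation is stated in three incompatible ways: 6 weeks after delivery, 6 weeks after discharge, and a last data phase closing 2 weeks after birth

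*Protocol*

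**What the plan says.** Three end points for the mother appear in the current protocol text.

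- **6 weeks after delivery.** Study design sets an "observation deadline of up to 14 days after birth for the new-born and 6 weeks postpartum for the mother". Data collection repeats this for the woman: collection is "planned from the diagnosis of a case in a pregnancy up to 6 weeks after delivery". Exclusion criteria removes women whose follow-up is lost before 6 weeks postpartum.
- **6 weeks after discharge.** The follow-up paragraph of Data collection says that "the medical history is consulted from the time the patient is discharged up to 6 weeks later in order to detect late postpartum complications". Substudy 3, Patients, has the same rule: "from the time the patient is discharged up to 6 weeks later in order to detect late postpartum complications". Both passages then name mastitis, endometritis and pulmonary embolism recorded in that period as outcomes of interest.
- **2 weeks after birth.** Data collection says that information on enrolled pregnant patients is gathered in two phases, the second being "the second phase, throughout the 2 weeks after birth". No later phase is described.

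Two other places mention 14 days without clearly setting a limit for the mother. The Abstract describes the registry "with an observation period of up to 14 days after delivery". A Substudy 1 table headed "Evaluation 14 days after delivery, N" contains a row for septic shock and maternal mortality.

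No passage says which rule prevails.

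**The concern.** The window determines which late complications are counted. Pulmonary embolism is a primary variable in Substudies 2, 3 and 4. Endometritis and mastitis are primary variables in Substudy 2, and the Substudy 3 Patients section names them as outcomes of interest.

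Two different problems follow, depending on which rule a site adopts. A short data phase loses late events altogether. A discharge anchor makes the time in which an event can be recorded depend on length of stay. The second problem matters most in Substudy 3, which compares infected women with controls and takes the COVID odds ratio as its only result of interest. With about 100 sites, it is realistic that different sites would follow different rules.

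**Working it through.** The protocol gives no figure to reproduce here, so the check compares the stated windows in days from delivery.

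**Inputs**
- Delivery-anchored window: 6 weeks = 42 days (Study design, Exclusion criteria, Data collection).
- Last data phase: 2 weeks = 14 days (Data collection).
- Discharge-anchored window: 42 + L days, where L is the number of days from delivery to discharge (Data collection, follow-up paragraph; Substudy 3, Patients).
- L is not given in the protocol. Values from 3 to 21 days are assumed for illustration.

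**Step 1: closing at 2 weeks**
- Unobserved part of the 42-day window: 42 − 14 = 28 days (days 15 to 42).
- Share: 28/42 = 67%.
- A record closed on day 14 cannot show whether follow-up was complete at 6 weeks, so the exclusion criterion cannot be applied.

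**Step 2: counting from discharge**

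| Assumed L (days) | Observation from delivery, 42 + L (days) | Ratio to 42 |
|---|---|---|
| 3 | 45 | 1.07 |
| 7 | 49 | 1.17 |
| 14 | 56 | 1.33 |
| 21 | 63 | 1.50 |

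A woman with an assumed 21-day stay is observed for 63/45 = 1.40 times as long as one with an assumed 3-day stay. This contrasts two hypothetical women. It does not estimate the difference between cases and controls.

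**Step 3: does the analysis absorb unequal time?** Substudy 3, Statistics, fits a multiple logistic regression to each outcome. As described, that model has no term for time at risk. The random intercepts under Heterogeneity tests address unmeasured differences between sites. They do not correct unequal follow-up between cases and controls within a site.

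**Step 4: which Substudy 3 outcomes are exposed?** Of the three late complications, only pulmonary embolism is in that substudy's visible variable table. Mastitis and endometritis are named in its Patients section. The full variable list is in a separate appendix that is not shown.

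**The case against.** The strongest defence is that the intended window is clear. Six weeks after delivery is stated three times, one of them an exclusion criterion that a 2-week record could not meet. The follow-up paragraph can be read as a review that starts at discharge and ends at the usual 6-week postpartum point. Even on the literal reading, every mother is observed for at least 42 days, so no event inside that window is missed. A data collection manual, not shown, may also set the schedule.

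This makes it likely that 6 weeks from delivery was meant, and it supports choosing that window. It does not remove the conflict: the discharge wording literally counts 6 weeks from discharge and appears twice, and the 2-week phase directly contradicts the paragraph before it. A statistical analysis plan could truncate dated events, but it could not recover data that sites stopped collecting after 2 weeks.

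Some stronger readings are tempting and are not supported:
- **That the Abstract and the Substudy 1 table are further contradictions.** Study design and Data collection assign 14 days to the new-born, so the Abstract is probably a compressed statement of that limit. A 14-day evaluation can sit inside a 6-week follow-up. The same symptom and severity block recurs in Substudies 2 and 3 without the 14-day heading, so it is unclear whether that heading governs the mortality row.
- **That the COVID odds ratio is biased upwards.** This needs cases to stay longer after delivery than controls. It is plausible, but cases are any PCR-positive woman whatever her symptoms, Substudy 3 draws on universal screening, and no lengths of stay are given. Extra observation time also does not translate one for one into extra events.

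**Conclusion.** The inconsistency is real and should be corrected. Followed as written, the 2-week phase leaves 67% of the stated 42-day maternal window uncollected and makes the 6-week exclusion unworkable. The discharge rule extends observation from delivery to 42 days plus length of stay.

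An effect on the Substudy 3 comparison is possible rather than shown. It depends on cases having longer postpartum stays than controls and on events occurring in the extra days. Its size cannot be computed because the protocol gives neither lengths of stay nor event timing. On the visible variable list it reaches the modelled odds ratio through pulmonary embolism, with mastitis and endometritis also exposed if they are modelled.

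**What to change.** Use the window that Study design, Exclusion criteria and Data collection already state, delivery to 6 weeks postpartum, for every mother, case or control.

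1. In the follow-up paragraph of Data collection and in Substudy 3, Patients, end maternal follow-up at 6 weeks after delivery. Count only events with onset by then, whatever the discharge date.
2. Record the onset date of each late complication if it is not already collected. The only date variable in the visible tables is the COVID-19 diagnosis date, and the full variable list is not shown.
3. In Data collection, extend the second phase to 6 weeks for the mother and keep 14 days for the new-born.
4. As clarifications, say in the Abstract that 14 days applies to the new-born, and say in the Substudy 1 table whether the 14-day heading covers the maternal mortality row.

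The cost is mainly wording, plus an onset-date field if there is none. Follow-up to 6 weeks is already planned. The small downside is that events after 6 weeks postpartum in women with long stays would no longer be counted.
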